#### Vocational adviser interviews

Once participant follow up is completed we shall interview a minimum of one adviser from each of the four boroughs. The aim of these will be
[1] to better describe treatment as usual with respect to advising service users about disclosure
[2]; to identify whether any contamination has occurred, either due to specific use of the DA or due to an increased focus on disclosure as a result of the study. The interview will therefore cover: knowledge of relevant legislation; attitudes about what service users should do with respect to disclosure; and practice with respect to what advice is given, the extent to which the advice is tailored to the client, and whether advice is given routinely versus in response to client requests.

Transcripts of the qualitative interviews will be coded using NVivo and thematic analysis will be used to identify participants’ perceptions of the impact of use of the DA and the impact of subsequent experience on intentions and behaviour regarding disclosure.

### Sample size

The heuristic sample size for pilot studies is 30 per group
[16]. However, we have elected to use a larger sample size so that we can test the effect of the DA with respect to a meaningful reduction in decisional conflict. The pre-post difference detected on the Decisional Conflict Scale in a preliminary study
[13] was found to be 16.5 points in the intervention group, with a standard deviation of 17.5. Estimating the effect of treatment as usual (i.e. vocational advisor standard support) at 4 points, this gives a standardised effect size of 0.71. Group sizes of 32 at the follow-up are needed to have 80% power to detect a difference of this size or greater at the 5% significance level. Further to test our exploratory hypotheses and refine our conceptual model, increasing from 64 (2×32) to 70 participants at follow up will allow logistic regression analysis to study relationships between baseline predictors and disclosure using 6 variables (plus the group variable), using the minimum of 10 per variable. Since we anticipate some loss to follow up at 3 months we shall aim to recruit 40 per group i.e. a total of 80 participants. Qualitative interview sample sizes are based on our expectations for the number of interviews required to cover a range of experiences and to reach the point where no new themes are identified in the analysis.

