### Analysis plan

The principal analysis of effectiveness will compare the primary and secondary outcome measures at 3 months. Changes in Decisional Conflict Scale scores are not prone to cut-off limits and are expected to be normally distributed. For both this and other normally distributed continuous outcome measures, an independent two sample t-test will be used to compare the change in effects (T1-T0) for the two groups (control and intervention). When continuous variables are predicted to be skewed (e.g. number of disclosures made), these can be tested using a two-sample Wilcoxon rank-sum test. The differences in number of disclosures made (T1-T0) for the two groups (control and intervention) can be compared. While items such as job offers and disclosure will be too infrequent to provide reliable comparisons, others such as appointments kept with the vocational adviser and submitted applications will be used as proxy measures for future employment outcomes. We will use confidence intervals for the effect sizes for these employment related activities to judge whether a full scale trial is indicated.

Attendance and dropout rates can be compared in terms of their baseline characteristics to see whether there are any obvious differences between retained and dropout participants. Adjustments to these analyses will be made to compensate for multiple testing. To study factors predicted by our model (see Figure
2) to be associated with disclosure we will use logistic regression. Each instrument will be studied to see whether it performs well enough for inclusion in a future trial. A correlation matrix will be formed from the items to calculate internal consistency and reliability, and to assess the appropriateness of forming composite or summary scores for previously defined sub-scales. Along with the histograms of each subscale, the data allow assessment of the appropriateness (particularly ceiling and floor effects) of the measures. Variables that perform well (and that appear not to be measuring the same thing) will be included in the logistic regression model, while adjusting for gender and diagnosis as these have been found to be associated with disclosure in other studies
[28,29].

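### The follow-up target of 70 counts ten participants per variable, not ten in the rarer disclosure outcome, so it does not support the seven-term logistic model

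*Protocol article*

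**What the plan says.** The Sample size section first sets 32 per group at follow-up for the Decisional Conflict Scale. It then says that "increasing from 64 (2×32) to 70 participants at follow up will allow logistic regression analysis". The outcome of that model is disclosure, its predictors are measured at baseline, and its size is justified by "using 6 variables (plus the group variable), using the minimum of 10 per variable". To allow for loss at 3 months, "we shall aim to recruit 40 per group i.e. a total of 80 participants".

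The Analysis plan returns to the same model. It screens the instruments and states that those performing well and not overlapping "will be included in the logistic regression model, while adjusting for gender and diagnosis". It does not say whether gender and diagnosis are among the six variables. Earlier in the same section, on comparing the two groups, it warns: "While items such as job offers and disclosure will be too infrequent to provide reliable comparisons". Neither section gives an expected disclosure rate or number of disclosers.

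**The concern.** The rule of ten per variable in logistic regression refers to the smaller of the two outcome groups, because that count limits the information about the coefficients. The article does not name the unit, but its figure works only if the unit is participants. If so, the model would have far fewer events per term than the rule asks for, and the one reason given for going from 64 to 70 would fall away.

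At stake are the predictor estimates. With few events per term, maximum-likelihood odds ratios are imprecise and on average lie too far from 1. At low event counts some fits do not converge because the data separate. The Sample size section gives this regression the job of helping to refine the conceptual model for the full-scale trial, so unstable associations could influence that design.

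**Working it through.** **Inputs from the article.** Sample size section: 70 at follow-up, 6 variables plus group, minimum 10 per variable, 80 recruited. Analysis plan: logistic regression of disclosure, adjustment for gender and diagnosis. Disclosure is taken as a yes/no outcome. **Assumed:** the disclosure proportion p, shown over a range because none is stated.

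**The article's figure.** 10 × (6 + 1) = 70. It reproduces exactly as participants × terms. Recruiting 80 with 70 retained implies a loss of 1 − 70/80 = 12.5%.

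**The rule in events.** Smaller class = 70 × min(p, 1 − p). This is largest at p = 50%, where it is 35. Then 35/7 = 5 per term, half the stated minimum. Above 50% the non-disclosers become the limiting class, so no value of p does better.

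Below, events per term = 70p/7, terms supported = the whole part of 70p/10, and N needed for 7 terms = 70/p, rounded up.

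| Assumed p | Disclosers in 70 | Events per term (7 terms) | Terms supported at 10 events each | N needed at follow-up for 7 terms |
|---|---|---|---|---|
| 50% | 35 | 5 | 3 | 140 |
| 30% | 21 | 3 | 2 | 234 |
| 20% | 14 | 2 | 1 | 350 |
| 10% | 7 | 1 | 0 | 700 |

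**Number of terms.** If gender and diagnosis are among the six, the model has 7 terms. If they are added, it has 6 + 1 + 2 = 9, taking diagnosis as a single term. With 9 terms the best case is 35/9 = 3.9 events per term, and N needed is 90/p: 180, 300, 450 and 900 at 50%, 30%, 20% and 10%.

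**Consequence for the estimates.** A simulation used 70 participants, 7 terms and 3,000 runs per rate. Assumed true effects were a log odds ratio of 0.693 for group and 0.5 for each of six standardised predictors. Runs that separated or failed were left out of the means.

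| Assumed p | Mean estimate, predictors (true 0.5) | Relative bias | Mean estimate, group (true 0.693) | Relative bias | Failed or separated |
|---|---|---|---|---|---|
| 50% | 0.605 | 21% | 0.799 | 15% | 0% |
| 30% | 0.613 | 23% | 0.827 | 19% | under 0.1% |
| 20% | 0.650 | 30% | 0.899 | 30% | 0.5% |
| 10% | 0.722 | 44% | 0.888 | 28% | 14% |

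Relative bias is the mean estimate divided by the true value, minus 1. The direction is the same in every row. The size varies with the coefficient and the rate, and would change with other assumed effects.

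**What is unaffected.** The decisional-conflict calculation gives (16.5 − 4)/17.5 = 0.71 and, with a two-sided t-test at 5%, 31.8 per group for 80% power. That rounds up to the stated 32. It does not depend on the regression.

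**The case against.** The best defence is that little hangs on this model. The article calls the hypotheses behind it exploratory, the Abstract places predictors of disclosure among the secondary analyses, and the Hypotheses section says hypothesis testing is not the main objective. That section also says the conceptual model will be examined through process evaluation and qualitative data, so the regression is one input among several. All of this stands, and it limits the severity. It does not rescue the sample-size statement, which says plainly that 70 permits a seven-term model under a rule that 70 cannot meet.

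Three stronger readings are tempting but not supported:

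- **At least ten terms, hence 100 participants even on the article's own count.** A reader might get there by adding all seven predictor instruments to gender, diagnosis and group. But the instruments are a candidate pool that the Analysis plan will screen, and the Sample size section limits the variables to six plus group. Four selected scores with gender and diagnosis would fit exactly. What remains is an ambiguity between 7 and 9 terms.
- **A direct contradiction in the Analysis plan.** The remark on infrequency concerns comparisons between the two arms, while the regression pools them. The remark does indicate few disclosers, which makes the shortfall worse, but the two statements are not strictly incompatible.
- **Every odds ratio will be inflated and wrong predictors will go forward.** Bias away from the null is an average tendency whose size rests on assumed effects. Selection of wrong predictors has not been shown.

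**Conclusion.** The point holds as a faulty sample-size justification. The multiplication is right, but the unit of the rule is wrong. Seventy at follow-up gives at most 5 in the rarer class per term for seven terms, and this needs no assumption about the disclosure rate. The figures of 1 to 3 per term rest on assumed rates of 10% to 30%, which fit the article's own expectation of infrequent disclosure but are not stated in it. The simulated bias is illustrative only.

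This should be fixed, but it is not critical. The analysis is exploratory, 32 per group for decisional conflict stands, and recruiting 80 remains defensible on other grounds.

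**What to change.** In the Sample size section, delete the claim that 70 supports seven variables. State the rule in events: 70 participants support at most 3 terms at 50% disclosure, 2 at 30%, 1 at 20% and none at 10%. Justify recruiting 80 by the need for 64 at follow-up with up to 20% loss (80 × 0.8 = 64).

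In the Analysis plan, do one of two things. Either limit the number of terms, group included, to what the observed smaller outcome class supports, or report each predictor with a confidence interval from a penalised (Firth) fit, described as descriptive. A fixed small model is not a safe substitute: group plus one predictor already has two terms, which exceeds what 20% disclosure supports. State also whether gender and diagnosis count towards the limit.

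The cost is a change of wording in two sections and fewer predictors examined jointly. No extra participants are needed.

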### Recruitment and randomisation

#### Ethics approval

The study has been approved by the National Research Ethics Service Committee East of England – Essex.

#### Recruitment

Employment advisers attached to community mental health teams and IAPT services will be asked to inform people on their caseload about the study by giving them a flyer summarising the main points of the study. With service users’ permission the adviser will pass on contact details of interested service users to the study research worker. The worker will contact the service user to determine their eligibility, provide further study information to those eligible, offer a period of time for consideration and document informed consent from those eligible and wishing to enter the study.

#### Sequence generation

Block randomisation with randomly varying block sizes will be used. We shall stratify by
[1] referral source i.e. primary vs. secondary mental health services, since these groups are likely to differ with respect to severity of illness, and
[2] by length of time out of work (less vs. more than 12 months), as this affects chances of regaining employment.

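### Randomisation is stratified by referral source and time out of work, but the named t and rank-sum tests ignore both factors, which costs precision wherever the strata predict the outcome

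*Protocol article*

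**What the plan says.** Under Sequence generation the protocol states: "Block randomisation with randomly varying block sizes will be used". It stratifies by "referral source i.e. primary vs. secondary mental health services, since these groups are likely to differ with respect to severity of illness", and "by length of time out of work (less vs. more than 12 months), as this affects chances of regaining employment".

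The Analysis plan then fixes the between-arm comparisons. For normally distributed continuous outcomes, "an independent two sample t-test will be used to compare the change in effects" between baseline and 3 months. For skewed variables, "these can be tested using a two-sample Wilcoxon rank-sum test". Neither test takes the stratification factors. The only covariates named anywhere belong to the separate logistic regression for disclosure, which is fitted "while adjusting for gender and diagnosis as these have been found to be associated with disclosure in other studies".

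For activities such as appointments kept and applications submitted, the same section says: "We will use confidence intervals for the effect sizes for these employment related activities to judge whether a full scale trial is indicated".

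**The concern.** Blocking within strata makes the arms nearly equal in stratum composition, so variation between strata largely drops out of the treatment difference. The standard error of a plain two-sample test does not know this: it still counts between-stratum variation as noise. If the strata predict the outcome, the reported interval is wider than the design warrants and the test rejects less than 5% of the time under the null.

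At stake is precision in a trial of 80 people. It matters most where the protocol leans on interval width, namely the employment-related activities that feed the decision on a full-scale trial. Time out of work was chosen as a stratifier for its bearing on employment.

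**Working it through.** **The plan's own figure first.** From the Sample size section, the effect is (16.5 − 4)/17.5 = 0.714, stated as 0.71. The normal approximation, n = 2(1.960 + 0.842)²/d², gives 30.8, so 31 per group, at d = 0.714, and 31.1, so 32, at d = 0.71. Exact two-sided t-test power at 32 per group is 0.803 (d = 0.714) or 0.798 (d = 0.71). The stated 32 per group reproduces. It already assumes an unadjusted test, so adjustment can only help it or leave it about the same.

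**Closed form.** Let R² be the share of within-arm outcome variance explained by the strata. With perfect balance, the true standard error is √(1 − R²) times the one that the two-sample test uses. Hence:
- excess interval width = 1/√(1 − R²) − 1, which is 2.6%, 5.4%, 11.8% and 19.5% at R² = 5, 10, 20 and 30%;
- true type I error ≈ 2Φ(−1.96/√(1 − R²)), which is 4.4%, 3.9%, 2.8% and 1.9%.

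**Simulation.** Unfinished blocks and loss to follow-up leave some imbalance, so the closed form slightly overstates the conservatism. The simulation used 80 randomised (Sample size section), 70 analysed (the follow-up target there), 1:1 allocation and a normal outcome. Assumptions not in the protocol are four strata of equal expected size, block sizes 2/4/6, loss at random, R² itself, and an effect of 0.6 SD for power. The unadjusted t-test was compared with a linear model on arm and the two factors.

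| R² (assumed) | Unadjusted interval wider by | Unadjusted type I error | Power, unadjusted | Power, adjusted |
|---|---|---|---|---|
| 0% | about 0% | about 5% | 70% | 70% |
| 5% | 2% | 4.7% | 70% | 71% |
| 10% | 5% | 4.2% | 70% | 74% |
| 20% | 12% | 3.2% | 72% | 79% |
| 30% | 20% | 2.3% | 73% | 84% |

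A repeat run gave type I errors of 4.7, 4.1, 2.9 and 1.9% at 5 to 30%, and interval widths and power within about one percentage point of the table. The adjusted model stayed close to 5% throughout.

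**At the protocol's own effect.** With 64 analysed, d = 0.714 and blocks of 2 or 4, power unadjusted versus adjusted was 81 v 82% (R² = 5%), 81 v 83% (10%), 84 v 88% (20%) and 82 v 91% (30%). In the same runs the rank-sum test had type I error 4.7, 4.5, 3.7 and 2.8%, so it is conservative in the same way. It was run on normal data; skewed counts were not simulated, nor was the van Elteren test.

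**In participants.** At R² = 20%, an unadjusted analysis needs 1/(1 − 0.20) = 1.25 times the sample for the same precision.

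**The case against.** The strongest case against is that the size is unknown and may be negligible. The protocol gives no variance share. At 5% or below, the interval is at most about 2 to 3% wider and power falls by no more than about two points. That stands.

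A reader might infer that the protocol calls both factors prognostic for its outcomes. It does not. Time out of work is tied to regaining employment. Referral source is tied only to severity of illness, with no outcome named. Neither is said to predict decisional conflict, stage of decision, empowerment or withdrawal. The t-tests also compare changes from baseline, which already remove stable differences between strata, so the share for the Decisional Conflict Scale could well be low.

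The employment link needs care too. The Analysis plan regards job offers as too rare for reliable comparison, and the intervals that inform the decision concern proxy activities. That time out of work predicts those activities is a reasonable inference, not a statement in the protocol.

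Finally, the Hypotheses section says that hypothesis testing is not the main objective, so a modestly conservative test does little harm in itself. That also stands for the tests. It does not answer the point about interval width, because the protocol makes those intervals a basis for deciding on the next trial. Nor is this a detail left to a later analysis plan: the protocol names the tests, and as named they take no covariates.

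**Conclusion.** The stated analysis does not use the stated design. The consequence is a possible loss of precision, conditional on the strata predicting the outcome: nothing at a variance share of 0%, negligible at 5%, and material from roughly 10 to 20% upward (intervals about 5 to 12% wider, and about 4 to 7 points of power at 0.6 SD). The variance shares are assumptions throughout.

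Two stronger readings are not supported. A reader might conclude that the trial's results would be biased or its false-positive rate inflated; the error runs the other way, and the treatment estimate stays unbiased. A reader might also conclude that every interval in the trial is certainly too wide; that would need a variance share for each outcome, which the protocol does not supply. The case is best for the employment-related activities and weakest for change in decisional conflict. It is a worthwhile improvement to the analysis, not a flaw that would overturn the trial's conclusions.

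**What to change.** In the Analysis plan, replace the two-sample t-test with a linear model for the same change score, containing arm and the two stratification factors with the values used at randomisation. Take the confidence intervals for the employment-related activities from the adjusted model where that model suits the variable. Where a rank test is kept for skewed variables, use the stratified (van Elteren) version, with a rule set in advance for merging sparse strata, since about 70 people over four strata may leave some small.

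The cost is a change of wording and two degrees of freedom. Both factors are already recorded in order to randomise, so no new data are needed, and the sample size is unchanged. If the factors prove uninformative, the simulations show essentially no loss.

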#### Allocation concealment

The sequence is concealed by the KCL Clinical Trials Unit from the research team.

#### Implementation

All randomisation will be undertaken via the independent Clinical Trials Unit (CTU) (which has been awarded full CTU registration by UKCRC) using an online randomisation system. They will not be provided with identifying information about service users. Participants will be enrolled by research workers blind to allocation while the CTU will inform only the researchers carrying out the intervention of allocation.

### Blinding

The blinded research workers are located in a separate office to those who are non-blind. It is not possible to keep participants blind to the intervention. To ensure the intervention occurs in as close a manner as possible to that in routine practice while minimising contamination, intervention group participants will be allowed to discuss the DA with vocational advisers but will be asked not to give them a copy. This means that vocational advisers cannot be blinded and therefore only the research team will be blind. At follow-up assessment, participants will be asked not to reveal their allocation status, and at the end of the interview the rater will record their guess about the service user’s allocation status. This will allow researcher blindness to be estimated.

### Analysis plan

The principal analysis of effectiveness will compare the primary and secondary outcome measures at 3 months. Changes in Decisional Conflict Scale scores are not prone to cut-off limits and are expected to be normally distributed. For both this and other normally distributed continuous outcome measures, an independent two sample t-test will be used to compare the change in effects (T1-T0) for the two groups (control and intervention). When continuous variables are predicted to be skewed (e.g. number of disclosures made), these can be tested using a two-sample Wilcoxon rank-sum test. The differences in number of disclosures made (T1-T0) for the two groups (control and intervention) can be compared. While items such as job offers and disclosure will be too infrequent to provide reliable comparisons, others such as appointments kept with the vocational adviser and submitted applications will be used as proxy measures for future employment outcomes. We will use confidence intervals for the effect sizes for these employment related activities to judge whether a full scale trial is indicated.

Attendance and dropout rates can be compared in terms of their baseline characteristics to see whether there are any obvious differences between retained and dropout participants. Adjustments to these analyses will be made to compensate for multiple testing. To study factors predicted by our model (see Figure
2) to be associated with disclosure we will use logistic regression. Each instrument will be studied to see whether it performs well enough for inclusion in a future trial. A correlation matrix will be formed from the items to calculate internal consistency and reliability, and to assess the appropriateness of forming composite or summary scores for previously defined sub-scales. Along with the histograms of each subscale, the data allow assessment of the appropriateness (particularly ceiling and floor effects) of the measures. Variables that perform well (and that appear not to be measuring the same thing) will be included in the logistic regression model, while adjusting for gender and diagnosis as these have been found to be associated with disclosure in other studies
[28,29].

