**Methods:**

In this single blind exploratory RCT in London, a total of 80 participants (inclusion criteria: age ≥18 years, on the caseload of a specialist employment adviser working with people with mental illness; referred to the adviser either from primary care via Improving Access to Psychological Therapies or secondary mental health service; currently seeking or interested in either paid or voluntary employment, and a Decisional Conflict Scale score of 37.5 or greater and stage of decision score 1–5) will be recruited from vocational advice services. After completing a baseline assessment, participants will be randomly assigned to one of two conditions (1) Use of the CORAL Decision Aid (DA) in addition to treatment as usual or (2) Treatment as usual. Those allocated to the DA condition will be given it to read and complete, and the researcher will be present to record the time taken and any content that causes confusion. Intervention participants may keep the decision aid but are discouraged from showing it to other service users to avoid contamination. Follow up interviews will be conducted at 3 months. Primary outcomes are: (i) stage of decision making score; (ii) decisional conflict scores and (iii) employment related outcomes. Secondary analyses will identify predictors of disclosure and qualitative analysis will explore the impact of the intervention.

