### Participants

Eligible service users will (i) be on the caseload of a specialist employment adviser working with people with mental illness; (ii) have been referred to the adviser either from the primary care based mental health service Improving Access to Psychological Therapies (IAPT) or secondary mental health care service; (iii) be aged 18 years or older; (iv) be currently seeking either paid or voluntary employment or interested in seeking paid or voluntary employment (v) have a Decisional Conflict Scale score of 37.5 or greater (showing at least moderate decisional conflict) and a Stage of Decision Scale score of 1–5 (showing the decision has not yet been reached); and (vi) give written, informed consent. We will exclude service users who have insufficient literacy in English to use the DA or who lack capacity to provide informed consent. Figure
1 shows the CONSORT flow chart for participants.

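### Decisional conflict is compared by an unadjusted t-test on change; adjusting the 3-month score for baseline would be more precise and would remove the effect of chance baseline imbalance

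*Protocol article*

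**What the plan says.** The Analysis plan section of the protocol article names the test for decisional conflict and for other normally distributed continuous measures: "an independent two sample t-test will be used to compare the change in effects (T1-T0) for the two groups (control and intervention". No covariate enters this comparison. The only covariates named anywhere in the section are gender and diagnosis, and they belong to the separate logistic regression for disclosure.

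Decisional conflict is one of three primary outcomes in the Abstract: "Primary outcomes are: (i) stage of decision making score; (ii) decisional conflict scores and (iii) employment related outcomes". Its baseline value is known for every participant, because entry requires people to "have a Decisional Conflict Scale score of 37.5 or greater (showing at least moderate decisional conflict").

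The Sample size section rests on the same change score. The preliminary pre-post difference "was found to be 16.5 points in the intervention group, with a standard deviation of 17.5". The control change is assumed: "Estimating the effect of treatment as usual (i.e. vocational advisor standard support) at 4 points". The section concludes that "this gives a standardised effect size of 0.71" and asks for 32 per group at follow-up for 80% power at the 5% level.

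The Sequence generation section stratifies on referral source and on time out of work. The baseline decisional conflict score is not a stratification factor.

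**The concern.** Subtracting the baseline score amounts to assuming that each extra point at baseline carries through to one extra point at 3 months. If the true slope is below 1, the subtraction over-corrects. Two things follow.

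- The change score carries variance that a fitted slope would remove, so the confidence interval is wider than the same data allow.
- If one arm happens to start higher, part of that difference enters the estimated effect. Randomisation does not balance the baseline score within strata, so with 32 to 40 people per arm an imbalance of a few points is ordinary.

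At stake is the precision of the decisional conflict estimate. The Sample size section enlarged the trial above 30 per group so that this effect could be tested, and objective (i) uses it to set parameters for a full trial. The validity of the test is not at stake.

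**Working it through.** **Inputs.** From the Sample size section: intervention change 16.5, control change 4, SD 17.5 (taken as the SD of change), 32 per group. The level is 5%; sidedness is not stated, and two-sided reproduces the stated size. The correlation rho between baseline (T0) and 3-month (T1) scores is not given, so 0.3, 0.5 and 0.7 are assumed.

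**Step 1: the plan's own figure.** Difference 16.5 − 4 = 12.5; d = 12.5/17.5 = 0.714. A two-sided t-based calculation needs 31.8 per group with d = 0.714, or 32.1 with d = 0.71. Power at 32 per group is 80.3%. The stated 32 reproduces. A one-sided test would need only 25.

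**Step 2: gain with equal SDs at T0 and T1.** The variance of the ANCOVA estimate relative to the change-score estimate is (1 + rho)/2. The effective SD is 17.5 × √ratio. Power comes from the noncentral t with 2n − 3 = 61 degrees of freedom. The planned test has a 95% CI half-width of about 8.75 points.

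| rho | Variance ratio | Effective SD | Power at 32 per arm | 95% CI half-width |
|---|---|---|---|---|
| 0.3 | 0.65 | 14.11 | 93.7% | 7.05 |
| 0.5 | 0.75 | 15.16 | 90.1% | 7.58 |
| 0.7 | 0.85 | 16.13 | 86.2% | 8.07 |

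**Step 3: allow for the entry cut-off.** Selecting people on baseline narrows the baseline SD. Under a linear model it leaves the slope b and the residual variance unchanged. Let b equal the unrestricted rho, and let k be the restricted baseline SD divided by its unrestricted value. In units of the unrestricted variance, the residual variance is 1 − b² and the variance of change is (1 − b)²k² + 1 − b². Hence

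ratio = (1 + b) / [(1 − b)k² + 1 + b].

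Example: b = 0.5, k = 0.8 gives 1.5/(0.32 + 1.5) = 0.82. The SD of change is held at 17.5.

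| Unrestricted rho | Ratio, k = 0.8 | Power | Ratio, k = 0.6 | Power |
|---|---|---|---|---|
| 0.3 | 0.74 | 90% | 0.84 | 87% |
| 0.5 | 0.82 | 87% | 0.89 | 85% |
| 0.7 | 0.90 | 84% | 0.94 | 83% |

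The gain is smaller than in Step 2 in every row.

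**Step 4: effect of chance imbalance.** A baseline difference of D points shifts the change-score estimate by (1 − b)D in size. With rho = 0.5 and equal SDs, the raw SD is 17.5/√(2 × 0.5) = 17.5, and the standard error of the baseline difference is 17.5 × √(2/32) = 4.4 points. A one-SE imbalance shifts the estimate by 0.5 × 4.4 = 2.2 points and a 1.96-SE imbalance by about 4.3, against a planned difference of 12.5. With k = 0.8 and the SD of change still 17.5, these shifts fall to about 1.8 and 3.6 points. ANCOVA removes the shift in expectation.

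**The case against.** The other side has a good case on several points.

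- **The planned test is sound and consistent with the sizing.** It matches the pre-post basis of the sample size, is unbiased over randomisations and has 80% power at 32 per arm. At the 35 per arm implied by 70 at follow-up it has about 84%. No required power is lost. This stands, and it limits the point to efficiency and to bias conditional on an observed imbalance.
- **This is a proof-of-concept trial.** The Hypotheses section puts hypothesis testing second, and the judgement on a full trial uses confidence intervals for employment-related activities. This lowers the stakes. It does not remove the value of a tighter estimate of decisional conflict, which objective (i) asks for.
- **An analysis plan that is not shown may add covariates.** It may, but the article states a specific unadjusted test, so the point concerns a stated choice and not an omission.

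Four stronger readings are tempting and are not supported.

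- **That the cut-off enlarges the gain by lowering rho.** This uses (1 + rho)/2 outside its equal-variance condition. Step 3 shows that truncation reduces the gain.
- **That regression to the mean biases the comparison.** Both arms pass the same cut-off and regress equally in expectation. Only chance imbalance remains.
- **That decisional conflict is the only outcome that sets the sample size.** The Sample size section also raises follow-up from 64 to 70 for the logistic regression of disclosure.
- **That the entry rule refutes the sentence "Changes in Decisional Conflict Scale scores are not prone to cut-off limits and are expected to be normally distributed".** That sentence is about changes. A lower limit on baseline does not itself bound change: someone entering at 37.5 can still fall 37.5 points, which is (37.5 − 16.5)/17.5 = 1.2 SD beyond the expected fall. The section also plans to examine floor and ceiling effects. There is no sufficient ground for asking that the sentence be deleted.

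**Conclusion.** The point holds as an improvement in precision, not as an error that invalidates the analysis. The direction is secure: apart from one degree of freedom, ANCOVA is never less precise than the change score, and the two tie only when the baseline slope is 1.

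The size is uncertain, because the document gives neither the correlation nor the baseline SD. With 17.5 as the SD of change and rho between 0.3 and 0.7, power at 32 per arm rises from 80% to between 86% and 94% if the two SDs are equal. It rises to about 83% to 90% if the cut-off narrows the baseline SD to 0.6 to 0.8 of its unrestricted value. Since the trial does select on baseline, the lower range is the safer one to quote. Protection against chance imbalance is worth roughly 2 points of the estimate for a one-SE imbalance at rho = 0.5.

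**What to change.** In the Analysis plan, replace the t-test on change with a linear regression (ANCOVA) of the 3-month score on arm and baseline score. Apply it to decisional conflict, empowerment and withdrawal, and report the adjusted difference between arms with its 95% confidence interval. Keep 32 per group and describe it as conservative under this analysis.

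The cost is one degree of freedom and a change of wording. No new data are needed, since the baseline score already serves eligibility and forms T1 − T0. The model also yields the baseline slope and the residual SD, which are useful for sizing a full trial.
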